## Methods

### Trial design

We will undertake a multi-centre parallel, superiority, open-label randomised trial in three publicly funded hospitals in India: Government Medical College Nagpur, Daga Memorial Women’s Hospital and Mahatma Gandhi Institute of Medical Sciences.

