### Randomization and masking

After the patient orally confirms her wish to participate in the trial, the research staff will open a sequentially numbered, sealed, opaque envelope containing the participant’s group. Gynuity Health Projects will generate the envelopes using a randomisation code based on a computerised pseudo-random number generator. Randomisation will be stratified by centre, with randomly determined block sizes of 4, 6 or 8. Neither the participating providers nor the participants will be blinded to the group assignment due to the complexity of titrating two separate uterotonics simultaneously.

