### Outcomes

The primary outcome will be caesarean birth, a core outcome used in the Cochrane Collaboration induction of labour generic protocol [12], as the induction of labour core outcome set [13] had not been published at the time of protocol development. A tble of assessments is shown in Table 1. The need for caesarean birth combines the efficacy of the induction (important when induction is being conducted for hypertension in pregnancy) with the safety of the induction process for mother and fetus. It is a particularly important outcome as caesarean birth poses a serious risk to maternal health in the context of the setting and hypertensive disease. Secondary outcomes will include measures of efficacy of the induction process (randomisation to birth interval; vaginal births within 12 and 24 h of randomisation; duration of hospital stay); additional outcomes to allow meta-analysis (start of induction to birth interval; cervix unchanged at 12 and 24 h after the start of cervical preparation; vaginal births within 12 and 24 h after the start of cervical preparation); maternal complications (uterine tachysystole (defined as > 5 contractions in 10 min), uterine hypertonus (defined as a single contraction lasting over 2 min); and hyperstimulation syndrome (tachysystole/hypertonus with associated fetal heart rate abnormalities); uterine rupture; instrumental vaginal delivery; severe hypertension and HELLP Syndrome; maternal vomiting, diarrhoea or fever; antibiotic use; postpartum haemorrhage (> 1,000 ml, or any bleeding leading to systolic blood pressure less than 90 mmHg or diastolic blood pressure less than 60 mmHg or blood transfusion)) and serious maternal complications (intensive care unit admission; septicaemia; pulmonary oedema; cerebral haemorrhage or oedema; renal failure; eclampsia and maternal death). Maternal satisfaction will be assessed using a ‘Mother Generated Birth Satisfaction Index.’ Health economic data will also be collected to allow a full economic analysis of the intervention.

**Table 1 Tab1:** Schedule of enrolment, interventions and assessments

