### Statistical analysis

The trial statistician will provide the Independent Data and Safety Monitoring Committee (IDSMC) with a blinded report every 6 months via email for safety monitoring and will conduct one planned formal interim analysis after 200 women have been recruited. The interim analysis will be for safety and for effectiveness but not for futility; stopping rules will be in accordance with O’Brien-Fleming rules [14] whereby the effective alpha level will be 0.0054 (z = 2.782) for the interim analysis and 0.0492 (z = 1.967) for the final analysis. The IDSMC will have the authority to request further interim analyses if indicated; in the unlikely event this should this occur, revised stopping rules based on the O’Brien-Fleming principles will be calculated according to whether the additional analyses are requested before or after the formal interim analysis at 12 months.

Safety reporting of Serious Adverse Reactions will occur from the period of randomisation until 48 h or discharge, whichever is sooner. Reporting procedures will comply with regulatory authorities in the United Kingdom and India. Trial monitoring will be performed by staff at Gynuity Health Projects on behalf of the sponsor in accordance with the MOLI trial monitoring plan. The research team will share important protocol modifications with relevant parties including investigators, IRBs, trial registries and trial participants as appropriate and in compliance with relevant laws and regulations.

The primary analysis will be performed according to the intention-to-treat principle. The primary outcome measure will be evaluated using binomial regression models, initially unadjusted and then after adjustment for important potential confounding variables and covariates. Binomial regression will be used for binary categorical measures, while ordinal regression will be used for multi-category variables. Count variables will use Poisson regression models and time measures using Cox proportional hazards regression models. All findings will be reported in accordance with the CONSORT guidelines for randomized trials.

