All regression models will be run unadjusted (i.e., with treatment group as the only independent/ predictor variable) and then re-run with adjustment for important potential confounder variables/ covariates. These include (but are not necessarily confined to) mother’s age, gestational age, cm dilatation before randomisation, receipt of magnesium sulphate in last 12 h, current anti-hypertensive use, time from hospital admission to randomisation of < 24 h, diastolic blood pressure at enrolment, proteinuria at enrolment, parity, and booked pregnancy. Other potential covariates will include variables found to differ by a clinically significant amount at baseline (post-randomisation) and measures identified as potentially affecting outcome during the study period. Subgroup analysis will be by site of delivery, parity and gestational age. Within the constraints of the O’Brien-Fleming stopping rules, overall statistical significance (across the interim and final analyses) will be set at the conventional 5% level for primary outcomes and p < 0.01 for secondary outcomes. A statistical analysis plan will be completed prior to prior to the first comparative monitoring report to be presented to the IDSMC.

The ISDMC will oversee the safety of participants in the trial. The terms of reference of the ISDMC will be developed separately, based on the principles developed by the DAMOCLES group. The ISDMC, who will have full access to the trial results analysed by allocation, will report directly to the TSC with recommendations about the conduct of the trial as well as whether to continue or stop the trial. The ISDMC will have the following independent voting members: [name] (London School of Hygiene and Tropical Medicine), [name] (Maulana Azad Medical College and Loknayak Hospital, New Delhi), [name] (Burnet Institute, Melbourne), and [name], (The University of Manchester).

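### Randomisation is stratified by centre, but the article does not commit to centre in the primary-outcome model; if caesarean rates differ between hospitals, a little precision is lost

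*Protocol article*

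**What the plan says.** All statements are in the Methods of the protocol article.

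- Trial design describes an "open-label randomised trial in three publicly funded hospitals in India".
- Randomization and masking: "Randomisation will be stratified by centre, with randomly determined block sizes of 4, 6 or 8".
- Outcomes: "The primary outcome will be caesarean birth".
- Statistical analysis: the primary outcome is analysed with "binomial regression models, initially unadjusted and then after adjustment for important potential confounding variables and covariates". Unadjusted is then defined, for all regression models, by "i.e., with treatment group as the only independent/ predictor variable".
- The covariates of the adjusted models are introduced with "These include (but are not necessarily confined to) mother’s age, gestational age, cm dilatation before randomisation" and continue with magnesium sulphate, anti-hypertensive use, time from admission, diastolic pressure, proteinuria, parity and booking status. That makes ten named covariates, and centre is not one of them. The same paragraph admits further covariates by two routes: a clinically significant difference at baseline, or identification during the study as potentially affecting outcome. It also says that an analysis plan will be completed before the first comparative report to the monitoring committee.
- Site is named once as an analysis factor: "Subgroup analysis will be by site of delivery, parity and gestational age".

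**The concern.** Blocking within centre forces the two arms to have nearly the same mix of hospitals, so differences in caesarean rate between hospitals drop out of the treatment comparison. A model with treatment as its only term does not know this. It still counts the between-hospital variation in its standard error. If hospitals differ, the interval is wider than it need be and the test rejects less often than its nominal level. The balance that stratification bought is then partly wasted.

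What is at stake is a small amount of precision on the primary outcome. The same treatment-only definition governs the ordinal, Poisson and Cox models for the secondary outcomes; the effect there was not quantified.

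**Working it through.** **Inputs from the article.** Sample size calculation: control caesarean rate 31%; (a) 90% power for 31% against 18.5%; (b) 80% power for 31% against 20%; two-sided alpha 0.05; 260 per arm. Statistical analysis: final-analysis limit z = 1.967, alpha 0.0492. Three centres.

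**Inputs assumed.** The article gives no rates by centre. Control rates are taken as 31% − d, 31% and 31% + d, with d = 0, 5, 10, 15 or 20 points. Centres are of near-equal size and arms are balanced within centre. The risk ratio is the same in every centre, no outcomes are missing, and there is a single test at the final limit. The treatment-only model is taken as log-binomial, because the article expresses its target as a relative risk.

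**Step 1: the article's own figure.** Per arm, with p̄ the mean of p₁ and p₂,

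n = [1.960·√(2p̄(1−p̄)) + z_β·√(p₁(1−p₁) + p₂(1−p₂))]² / (p₁−p₂)²

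- (a) p̄ = 0.2475, z_β = 1.2816: n = 248.4, and 265 with continuity correction.
- (b) p̄ = 0.255, z_β = 0.8416: n = 245.3, and 264 with continuity correction.

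Both are within 2% of the stated 260. Without the correction, power at 260 per arm is 91.3% for (a) and 82.2% for (b). The sample size is reproduced.

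**Step 2: excess standard error under no treatment effect.** The treatment-only model uses the total variance p(1−p) = 0.31 × 0.69 = 0.2139. With stratified allocation the variance that matters is the within-centre part, 0.2139 − 2d²/3. The ratio of model-based to true standard error is R = √[0.2139 / (0.2139 − 2d²/3)], and the actual two-sided error is 2[1 − Φ(1.967·R)].

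| d (points) | 2d²/3 | within-centre variance | R | type I error |
|---|---|---|---|---|
| 0 | 0 | 0.2139 | 1.000 | 4.92% |
| 5 | 0.0017 | 0.2122 | 1.004 | 4.83% |
| 10 | 0.0067 | 0.2072 | 1.016 | 4.57% |
| 15 | 0.0150 | 0.1989 | 1.037 | 4.14% |
| 20 | 0.0267 | 0.1872 | 1.069 | 3.55% |

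**Step 3: simulation, 200,000 trials per scenario.** Two treatment-only tests (Wald on the log risk ratio, and the pooled two-proportion z-test) are set against a centre-stratified Cochran-Mantel-Haenszel (CMH) test, all at alpha 0.0492.

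Power for 31% against 20%:

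| d (points) | Wald | pooled z | CMH | CMH gain |
|---|---|---|---|---|
| 0 | 81.8% | 82.2% | 82.1% | none attributable to centre |
| 5 | 81.9% | 82.3% | 82.4% | 0.1 to 0.5 |
| 10 | 82.1% | 82.4% | 83.0% | 0.5 to 0.9 |
| 15 | 82.6% | 83.0% | 84.2% | 1.3 to 1.6 |
| 20 | 82.9% | 83.3% | 85.7% | 2.4 to 2.8 |

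The Wald test is already 0.3 point below CMH at d = 0. That gap is choice of test, so the pooled column is the cleaner comparison.

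Simulated type I error, Wald / pooled / CMH: 4.4 / 4.6 / 4.9% at d = 10, and 3.4 / 3.6 / 4.9% at d = 20.

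For 31% against 18.5%, Wald against CMH: 91.3% against 91.8% at d = 10, and 92.2% against 93.7% at d = 20. A delta-method approximation puts this scenario at 89.7% with d = 0, identically with and without centre. That small difference from the simulation is therefore approximation and not an effect of omitting centre.

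**The case against.** The strongest reply has three parts.

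**The covariate list is open and a plan is to follow.** A reader might infer that the article excludes centre from the adjusted model. It does not. The final covariate set is commonly left to the analysis plan, and centre may be named there. This stands for the adjusted model. It does not reach the unadjusted model, whose single term is fixed in so many words. Nor do the two stated routes for adding covariates lead naturally to centre: stratified blocking makes a baseline imbalance in centre very unlikely, and the other route depends on what is seen during the study, whereas a design factor can be named in advance.

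**The loss is conditional.** A reader might infer that standard errors are too large and power is lost as a matter of fact. The documents do not support that. They give one control rate, 31%, and none by hospital. With equal rates nothing is lost, and at ±5 points the loss is barely visible. This stands.

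**The effect is small and in the safe direction.** A reader might infer that the test is invalid or the sample size undermined. Neither follows. Type I error goes down, and in the simulations the treatment-only tests keep at least the stated 80% and 90% power at every spread examined. This also stands.

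Two further limits apply. The adjusted model was not simulated; covariates such as parity, dilatation and gestational age may already absorb part of any centre difference. And site is at least recognised as an analysis factor, though a subgroup analysis does not put it into the primary-outcome model.

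**Conclusion.** The point holds as a minor one. The treatment-only model omits the stratification factor, and the article does not commit to centre in the adjusted model. The cost depends on how far hospitals differ: nil if they do not, at most about 1 power point for spreads up to ±10 points, and just under 3 at ±20, with a test that becomes conservative and never liberal.

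These figures rest on the assumed centre rates, near-equal centre sizes, a common risk ratio and a single final test. The direction follows from the design; the size cannot be known from the documents.

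**What to change.** In the analysis plan or the next protocol version, state that the primary-outcome model contains treatment and centre, with centre as a three-level fixed effect. A centre-stratified Mantel-Haenszel risk ratio would serve equally well. Add centre to the named covariates of every adjusted model, and report the treatment-only model as a sensitivity analysis.

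The cost is a line of wording. Centre is known for every woman because allocation is stratified by it, so no patients or data are added. The change is best made before any comparative data are seen.

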## Discussion

Labour induction is one of the most commonly performed obstetric procedures and increasingly common worldwide. In India, almost 1 in 6 deliveries are induced [15]. However, evidence documenting women’s experience and perceptions of the labour induction process and specific cervical ripening and augmentation agents is limited. Most qualitative studies of women’s experience have been conducted in North America and Europe [16, 17]. To help address this gap, our study has employed multiple methodologies – including the utilisation of a mother-generated birth satisfaction index – to improve the recording and understanding of Indian women’s birth priorities and experiences. The use of misoprostol, an oral method for augmentation, has the potential to improve the patient experience by improving women’s mobility during labour. Together with the data from the mother-generated birth satisfaction index, a planned sub-study will undertake semi-structured interviews before the start of the induction and after delivery with a sub-set of women, in order to understand the priorities, experiences and acceptability of induction of labour for women and explore any differences between the two randomized study groups.

We have also planned three additional analyses to help understand the implications of the research findings for the broader health care system. First, as part of the planned qualitative study, our research team will conduct focus group discussions with health care workers at the recruitment sites both before and 4–6 months into the randomised trial. We aim to improve understanding of the feasibility, usability and acceptability of the different induction regimes to health care professionals and to explore potential barriers and solutions for implementing research findings into clinical practice.

Second, we have also planned an economic evaluation to assess patterns and levels of resource utilisation associated with each patient included in the two arms of the randomised trial of induction techniques. The analysis will help identify any variations in resource use (and overall health care expenditure) between the two treatment groups. Finally, we will also undertake a survey of health workers practicing in public health facilities in the two districts where the recruiting hospitals are located to enhance our understanding of provider knowledge, attitudes and practices related to intrapartum uterotonic use. Together these additional analyses will help to contextualise the findings from this randomised trial, improving our understanding of how they can be best implemented and disseminated to improve Indian women’s birth experience during induction of labour.

## Data Availability

The data from this study will be confidential until the database is closed at the end of the study. Following this the study investigators will have exclusive access to the data until the publication of the results in a journal. Once this has happened, the database will be open to other researchers upon request. Open access databases will also be sought so as to maximise the availability of our research data with as few restrictions as possible, in line with MRC and Wellcome Trust policy. The consent form will include a clause for the woman to give permission for her anonymous data to be used for future research studies.

## Abbreviations

ARM: Artificial rupture of membranes
IDSMC: Independent Data Safety Monitoring Committee
RR: Relative Risk
